### 2.2. Participants, Recruitment and Sample Size Calculation

A sample of 62 women with CNSNP were recruited between 30 and 65 years old from the community in Guarda, Portugal. Participants were recruited through an online google form, with a questionnaire in Google Docs format, which was disseminated through social network postings (Facebook and Instagram) and the sending of institutional emails from Polytechnic Institute of Guarda to its workers. There were two physiotherapist assessors, who initially assessed participants that responded to the advertisements, and they were different from the physiotherapists who performed the interventions in both groups. In the first visit, the participants provided oral and written forms of all necessary information about the trial, including the study purpose and procedure. After voluntarily signing the informed consent statement, if through a detailed interview they met all inclusion, exclusion, and withdrawal criteria (Table 1), they enrolled into the trial to begin with an initial evaluation with the assessors.

The sample size calculation has been made based on the potential modification of the primary outcomes, neck pain intensity, and neck disability (NPRS and the NDI-PT) from baseline to final assessments. For repeated measurements of the estimated sample size, accepting an alpha risk of 0.05 and a beta risk of 0.2 in a two-sided test, 26 subjects were necessary in the first group and 26 in the second to recognize a statistically significant difference greater than or equal to 2 units (SD = 1.75) (NPRS) or 7 units (SD = 6) (NDI), and to detect small differences in standardized means between groups (Cohen’s d = 0.8), since the intervention with therapeutic exercise is known to have a beneficial effect and we want to assess whether the intervention with GPR has similar or even greater effects. Finally, considering a 15% loss rate during the study, and in order to end up with a sample of 52 subjects, based on the power analysis results, the final sample to be recruited was 62 subjects, 31 in each group. The sample size calculation was made with the software “PASS 15 (NCSS statistical software)” and “The R Project for Statistical Computing”.

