### 2.8. Statistical Analysis

Data were analyzed by using the IBM-SPSS software package (version 23.0). Descriptive data analysis was reported by groups as means ± standard deviation for numeric variables and as frequencies and percentages for categorical variables. In the graphical representation, bar graphs by groups were used for numeric variables, and pie charts were used to represent categorical variables. The main change from baseline to 4 weeks of treatment will be calculated using an intention-to-treat analysis for each outcome measure.

Two-way repeated measures ANOVA were performed. Group factors, as age range, were considered as categorical variables in the statistical model, such as potential covariates, and the Time factor will be used to take into account the two pre-intervention (baseline) and the intermediate and final data in the intervention (2 and 4 weeks of treatment). The interaction between the two factors on the dependent variables was analyzed. When the interaction was statically significant, follow-up tests (post-hoc Sidak test) were performed to determine how the within-participant factors affected the dependent variables, and it could be used as a covariate in the model. The post-hoc Sidak test was calculated to determine which pairs of means have significant differences.

Correlations with Pearson’s r coefficient were determined to analyze whether the values of two or more numeric variables change in conjunction or are related at some time point of the study.

The level of significance for the statistical tests were set at *p* ≤ 0.05 with a confidence interval of 95%.

In order to focus on clinical relevance or clinically worthwhile effects, and assess the magnitude of the change in the result variables, the effect size of both treatments for the group × time repeated-measures ANOVA model were calculated as the partial eta squared (ŋp^2^) when significant, considering 0.01 small, 0.06 medium, and more than 0.14 large effect sizes, and we could use the Cohen d for any pairwise comparisons, when applicable.

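### The stated 80% power is for one unadjusted two-sided between-group test, but section 2.8 compares means only after a significant group × time interaction and then by Sidak, so the power is not tied to the planned analysis

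*Protocol article*

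**What the plan says.** **Sample size (section 2.2).** The calculation is made "accepting an alpha risk of 0.05 and a beta risk of 0.2 in a two-sided test", and "26 subjects were necessary in the first group and 26 in the second". The effects named are differences "greater than or equal to 2 units (SD = 1.75) (NPRS) or 7 units (SD = 6) (NDI"), and the section adds that the trial is sized "to detect small differences in standardized means between groups", with Cohen's d given as 0.8. It is introduced with the words "For repeated measurements of the estimated sample size", but no within-person correlation is given. Neither a multiplicity allowance nor a preceding interaction test is mentioned. A 15% loss takes 52 evaluable women to 62 recruited.

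**Analysis (section 2.8).** The change from baseline to 4 weeks is called the main change, by intention to treat. The test procedure is then a two-way repeated-measures ANOVA. The group × time interaction is examined and, if it is significant, Sidak follow-up tests are run to see how the within-participant factors act. The section continues: "The post-hoc Sidak test was calculated to determine which pairs of means have significant differences". It closes with a general threshold: "The level of significance for the statistical tests were set at" p ≤ 0.05, with 95% confidence intervals.

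**Outcomes and visits (sections 2.4 and 2.6.1).** The primary outcomes are within-group change and between-group differences in pain and disability at the assessment times. Pain (NPRS) is measured at four visits. Disability (NDI) is not measured at the 2-week visit, so it has three.

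**The concern.** The introduction asks which of two exercise methods is superior, and section 2.2 powers that question as one comparison of two groups. Section 2.8 describes only two steps that could answer it: the interaction test and the post-hoc pairs. A two-step procedure in which both steps must succeed cannot have more power than the second step alone, and a Sidak adjustment lowers it further if the between-group contrast shares a family with other comparisons.

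Two things are at stake. A null result would be read as coming from a test with 80% power at d = 0.8 when the procedure used may have had less. And a 4-week difference with an unadjusted p a little below 0.05 could be reported as positive or not, depending on whether the interaction was significant and on which pairs were put into the Sidak family.

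**Working it through.** **1. Reproduce the plan's figure.** Inputs from section 2.2: two-sided alpha 0.05, power 0.80, d = 0.8, equal groups. For a two-sample t test the noncentrality is d × √(n/2). With n = 26 it is 0.8 × √13 = 2.884 on 50 degrees of freedom, and power is 0.807. With n = 25 power is 0.791, and the solved n is 25.5, so 26 is reproduced. Inflation for loss: 26/0.85 = 30.6, hence 31 per group and 62 in all.

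The raw differences, with their SDs taken as the SD of the compared quantity, give d = 2/1.75 = 1.143 and 7/6 = 1.167. These need only 14 and 13 per group and do not reproduce 26. The operative input is therefore d = 0.8 in a single unadjusted test.

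**2. Power of the interaction test.** The document gives no correlation or effect profile, so these are assumptions:

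- compound symmetry with within-person correlation ρ;
- d = 0.8 on the change from the second pre-intervention visit to 4 weeks, so the mean difference is 0.8σ√(2(1−ρ));
- no group difference at either pre-intervention visit;
- a fraction f of the 4-week effect present at 2 weeks (NPRS only).

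With p_t the effect at visit t as a fraction of the 4-week effect, the noncentrality of the interaction F test is

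λ = n × d² × Σ(p_t − p̄)² = 26 × 0.64 × Σ(p_t − p̄)² = 16.64 × Σ(p_t − p̄)²

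ρ cancels under this scaling. Degrees of freedom are 3 and 150 for NPRS, and 2 and 100 for NDI.

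**3. Power when both steps must succeed.** The joint power was simulated with 40,000 trials per row, 26 per group, the interaction at 0.05 and the 4-week change contrast at 0.05 with no Sidak penalty.

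| Outcome, profile | Σ(p_t − p̄)² | λ | Interaction alone | Interaction and contrast |
|---|---|---|---|---|
| NPRS, f = 0 | 0.750 | 12.48 | 0.84 | 0.75 |
| NPRS, f = 0.25 | 0.672 | 11.18 | 0.80 | 0.73 |
| NPRS, f = 0.5 | 0.688 | 11.44 | 0.81 | 0.74 |
| NPRS, f = 0.75 | 0.797 | 13.26 | 0.87 | 0.76 |
| NPRS, f = 1 | 1.000 | 16.64 | 0.94 | 0.79 |
| NDI | 0.667 | 11.09 | 0.84 | 0.77 |

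The ungated contrast stays at 0.81 throughout. An independent run of the same calculation gave 0.74 to 0.79 for NPRS and 0.76 to 0.78 for NDI.

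**4. Sensitivity to scaling.** If d = 0.8 is put on the 4-week score instead of the change, ρ matters. At ρ = 0.3, 0.5 and 0.7, with f = 0.5 for NPRS, the joint power is 0.59, 0.69 and 0.79 for NPRS and 0.64, 0.73 and 0.79 for NDI.

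**5. Sidak, if it applies to the between-group contrast.** The per-comparison level is 1 − 0.95^(1/m) for a family of m. The protocol does not give m, so a range is shown (ungated, 26 per group, d = 0.8).

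| m | Per-comparison level | Power | n per group for 80% |
|---|---|---|---|
| 1 | 0.0500 | 0.81 | 26 |
| 2 | 0.0253 | 0.72 | 31 |
| 3 | 0.0170 | 0.66 | 35 |
| 4 | 0.0127 | 0.62 | 37 |

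One GPR versus STE comparison per visit would be m = 4 for NPRS and m = 3 for NDI. Comparing the two groups at one visit only is m = 1 and costs nothing.

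**The case against.** A reader might infer more than the text supports, in three ways.

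- **That the two sections use different alphas.** They do not. Both state 0.05, and Sidak holds the family-wise level at 0.05. A smaller per-comparison threshold is not a second stated alpha.
- **That the Sidak comparison decides the trial.** Nothing says so. Section 2.8 makes it a follow-up, chiefly on the within-participant factor. On a plain reading the interaction test may itself be the answer to GPR versus STE, and alone it reaches about 0.80 or more under the change-score assumptions above.
- **That power collapses to roughly 56% or 36%.** Those values come from families of 6 and 28. Six is the number of pairs among four visits, and the GPR versus STE contrast is not one of them. Twenty-eight is all pairs of eight group-by-visit means, a family the protocol never describes and one that NDI, with three visits, does not have.

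It can also be said that section 2.2 describes its calculation as one for repeated measurements, and that the raw differences read literally (d = 1.14 and 1.17) leave power at 0.95 or more even for m = 3. If nobody is lost, 31 per group gives 0.87 unadjusted and 0.80 for m = 2. Finally, an article may leave the list of post-hoc pairs to an analysis plan.

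All of this limits the size of the problem, and the absent list of pairs is not held against the protocol. What remains is that two procedures are both written down and do not match. The literal raw effects do not rescue the stated figure, because they do not yield 26 per group.

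**Conclusion.** The concern holds in a limited form. The 80% in section 2.2 belongs to one unadjusted two-sided between-group test at d = 0.8. Section 2.8 reaches a comparison of means only through a significant interaction and then a Sidak test, so the power statement does not describe the planned analysis.

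If both the interaction and the 4-week contrast are required, power falls from 0.81 to about 0.74 to 0.79 for NPRS (0.73 in the least favourable profile tried) and 0.76 to 0.78 for NDI. This rests on d = 0.8 on the change, compound symmetry and the profiles listed. The range widens to 0.59 to 0.79 if d is scaled on the score. If the contrast sits in a Sidak family of two or more, the ungated figure is 0.72 or less. If the interaction alone decides, or if the contrast is a single ungated pair, 80% can be met. The loss is therefore conditional and mostly modest. The mismatch itself is not conditional.

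**What to change.** Add to section 2.8 that, for each primary outcome, the GPR versus STE difference in change from baseline to 4 weeks is tested once, two-sided at the alpha used in section 2.2, and reported with its 95% confidence interval. State that this test does not depend on a significant interaction and lies outside the Sidak family. Keep the interaction and the Sidak pairs as secondary description of the time course. This agrees with the change that section 2.8 itself calls the main one and with the test that section 2.2 powered.

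If the gated procedure is kept as the primary test, restate the power in section 2.2 for that procedure, giving the assumed correlation, the effect profile and the size of the Sidak family.

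The first option costs one sentence. The second costs a recalculation and probably a lower power figure. Neither needs more participants or data.

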GPR is based on the concept that postural muscles are organized to act in concert with each other as “muscle chains” located anterior and posterior to the spine [55,61,67,74], and it has been hypothesized that some specific clinical presentations are caused by shortened muscles or “muscle chain retractions” [61,63,67]. Treatment with an active muscle stretching method exerts physiological effects not only at spinal but also at motor cortical level, increasing the amount of intracortical inhibition and/or reducing intracortical excitation, and induces a significant reduction of motoneuron excitation, which is caused by both pre- and postsynaptic mechanisms [62]. Moreover, according to the GPR basic principles of causality, globality, and muscle chain distribution [57,61,63,66,74], all of them containing the regional interdependence model of musculoskeletal dysfunction [80], the increased cortical inhibition following GPR was not limited to a specific muscle but tended to extend to segmentally related peripheral muscles [62].

However, there are few studies following the treatment of patients with chronic nonspecific neck pain with GPR, and no study has yet compared GPR with STE in NSNP and their effects on neuromuscular patterns or efficiency using an electromyographic assessment, as well as the correlations of this with pain, disability, standing postural control, and psychosocial components [55,56].

Considering that GPR is a therapeutic intervention with an approach based on an integrated idea of the muscular, it assesses and aims to act on the role and status of the functional groups of muscles responsible for posture and its alterations that form the muscle chains [55,56,66,67,81]. Most previous studies address pain and functionality as outcome variables [55,56], and very few address specific variables of postural balance [82], muscle efficiency with EMG [70], or psychosocial factors associated with pain such as kinesiophobia [67].

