We considered the conclusions and indications of previous studies, based on the need for high-quality prospective clinical trials comparing GPR with effective treatment strategies for neck pain, such as manual therapy or therapeutic exercises [15,55,56,59]. Taking into account what has been described above, we considered it interesting to contribute more knowledge regarding the use in clinical practice of a wider variety of methods based on exercise and manual therapy. In our study we address the GPR, which due to the heterogeneity of the results of some studies, it presents some lack of evidence that we address in our study, on parameters in the application protocols and the effects on some outcome variables not sufficiently assessed in previous studies as patterns or neuromuscular efficiency, postural control and psychosocial factors, and also compare these effects with those caused by other therapies in this study factor (CNSNP).

Therefore, this randomized parallel clinical trial will aim to evaluate the benefits of GPR and STE, as two different exercise modalities, the former more dynamic [46,47,49,54], and the latter more static/postural [61,73,77], considering that both have mechanisms of action targeting symptomatology [46,47,55,56] and muscle efficiency [46,54,68]. So, pain, disability, postural control, neuromuscular function, and the correlations between them will be assessed in women with chronic non-specific cervical pain. The primary objective is to investigate the most effective and efficient intervention to improve neck pain intensity and disability. More concretely, we will evaluate if a global postural exercise method, such as GPR, or a specific therapeutic exercise has a superior effect. The secondary objective is to assess the effectiveness of the two interventions on cervical range of motion (CROM), pressure pain threshold (PPT) in the cervical region, kinesiophobia, pain catastrophizing, standing postural control, and neuromuscular efficiency of superficial cervical flexor muscles.

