#### 2.6.1. Primary Outcome Variables

The primary measured outcomes of the study will be the change within groups and the differences between groups of the neck pain intensity and the neck disability at the assessment times.

Neck pain intensity

Neck pain intensity will be measured using a numerical pain rating scale (NPRS). This is an 11-point scale ranging from 0, which represents one pain extreme (e.g., “no pain”), to 10, which represents the other pain extreme (e.g., “pain as bad as you can imagine” and “worst pain imaginable”) [95]. The subject is instructed to select the number that best represents the mean of their pain in the last week. Evidence suggests that the perception of pain intensity in subjects with chronic pain must be analyzed by NPRS, and it has been demonstrated to be a valid and reliable scale [96,97]. NPRS has a high test–retest reliability and responsiveness when applied intra-observer reliability of (r = 0.76) in patients with mechanical neck pain [97] and in both literate and illiterate patients with rheumatoid arthritis (r = 0.96 and 0.95) [98]. NPRS also has a high validity with visual analogue scale (VAS) in patients with rheumatic and other chronic pain conditions (pain > 6 months) (correlations range from 0.86 to 0.95) [95], and a high convergent validity with VAS and verbal rating scale (VRS) (r = 0.82–0.92) [99]. Chronic pain patients prefer the NPRS over other measures of pain intensity due to its comprehensibility and ease of completion [99,100].

Neck Disability

We will measure the neck disability associated with pain using the Portuguese version of the neck disability index (NDI–PT), which is valid and reliable with excellent internal consistency (Cronbach’s alpha = 0.95). NDI–PT has a high test–retest reliability with an ICC = 0.91 [101,102], and NDI also has a highly convergent validity with a variety of pain scales (r = 0.40–0.71) [101]. NDI–PT is a patient-completed, condition-specific functional status questionnaire with 10 items including pain, personal care, lifting, reading, headaches, concentration, work, driving, sleeping, and recreation. Each section is rated on a scale of 0 to 5, where 0 means “painless” and 5 means “worst pain imaginable.” The points obtained are added to a total score between 0 and 50. The NDI-PT scores are presented as a percentage of the maximum score, 0–8% without disability; 10–28% mild; 30–48% moderate; 50–64% serious, and 70–100% complete disability [103,104].

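### Unadjusted Pearson's r is named for two different questions, joint change and association at a visit, without saying what is correlated for each or allowing for randomised arm

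*Protocol article*

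**What the plan says.** The Introduction includes correlation in what the trial will assess: "So, pain, disability, postural control, neuromuscular function, and the correlations between them will be assessed in women with chronic non-specific cervical pain". A little earlier, in describing what no study has yet done, it lists effects on neuromuscular efficiency "as well as the correlations of this with pain, disability, standing postural control, and psychosocial components".

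Section 2.8 gives the method in one sentence. Pearson's r is to be used to "analyze whether the values of two or more numeric variables change in conjunction or are related at some time point of the study". No other correlation method is named. The sentence mentions no change score, partial correlation, or stratification or adjustment by arm. The same section sets p ≤ 0.05 for all tests. Its repeated measures ANOVA treats each outcome separately, so it says nothing about how two outcomes move together.

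Sections 2.4 and 2.6 show what data exist. Every outcome is measured at both pre-intervention visits and at 4 weeks. Only pain intensity, CROM and PPT are measured at 2 weeks. Sections 2.5 and 2.6 treat the second pre-intervention visit as baseline.

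**The concern.** Whether two variables are associated at a visit and whether they change together have different null hypotheses. Two traits that differ stably between women correlate at every visit even if their changes are independent. Conversely, linked changes can be nearly invisible in the levels. One method named for both, with the quantity left open, allows a correlation of levels to be reported as joint change.

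The second problem remains even if change scores are meant. After treatment starts, r computed over all women mixes two things: linkage within individuals, and the difference between arms. If one arm does better on both variables, r is pushed away from zero without any relation within either arm. An improvement common to both arms does no harm, because r removes the overall mean. Only a between-arm difference matters.

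At stake is the reading of exploratory results, such as whether neuromuscular efficiency or balance changed along with pain.

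**Working it through.** **Inputs from the protocol.** Section 2.2 gives 26 completers per arm (52), 62 recruited, 15% loss, d = 0.8, and NPRS and NDI differences of 2 (SD 1.75) and 7 (SD 6), "accepting an alpha risk of 0.05 and a beta risk of 0.2 in a two-sided test". Section 2.6.1 gives 0.40 as the low end of the correlation between NDI and pain scales.

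**The plan's own figure.** A two-sample t-test at d = 0.8 needs 25.5, so 26 per arm (power 80.7%). Then 52/(1 − 0.15) = 61.2, so 62. The stated size reproduces. The article gives no figure for the correlation analysis.

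**Assumptions.** All other inputs are assumed: the intraclass correlation (ICC, the stable between-woman share of variance), the SD of change, the baseline correlations other than 0.40, and the arm difference for pairs other than NPRS and NDI. Rejection rates come from simulation with 20,000 trials per setting, equal arms, two-sided 0.05. At N = 52 the critical |r| is 2.009/√(50 + 2.009²) = 0.273.

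**Step 1. Levels do not answer the change question.** Give two variables baseline SD 1 and correlation 0.4, and independent changes with SD s. The correlation of 4-week levels is 0.4/(1 + s²).
- s = 0.6: 0.29, significant in about 57% of trials
- s = 0.8: 0.24, about 42%
- s = 1.0: 0.20, about 29%

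The arm-adjusted correlation of changes is significant in 5%. Now reverse it: unrelated baselines and changes correlated 0.5. The level correlation is 0.5s²/(1 + s²) = 0.13, 0.20 and 0.25, with power 15%, 29% and 44%, against 97% for arm-adjusted changes.

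**Step 2. Pooling the arms.** Take two variables with SD 1, unrelated within arm, both shifted by d in one arm at 4 weeks. The shift adds d²/4 to the covariance and to each variance, so:
- levels: r = (d²/4)/(1 + d²/4)
- change scores: r = (d²/4)/(2(1 − ICC) + d²/4)

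At d = 0.8 and ICC 0.7 these are 0.16/1.16 = 0.14 and 0.16/0.76 = 0.21.

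| d on both | r, levels | Significant, levels (N = 52 / 62) | r, change | Significant, unadjusted change (N = 52 / 62) | Change, arm-adjusted |
|---|---|---|---|---|---|
| 0.5 | 0.06 | 7% / 7% | 0.09 | 10% / 11% | 5% |
| 0.8 | 0.14 | 17% / 19% | 0.21 | 33% / 38% | 5% |
| 1.14 (= 2/1.75) | 0.25 | 44% / 51% | 0.35 | 78% / 85% | 5% |

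The change-score columns use ICC 0.7. At ICC 0.5 the two formulas coincide; above 0.5 change scores are the more affected, below it the less.

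**The case against.** The strongest objection is that the sentence does not tie r to single-visit values for the change question. The reference to a time point belongs most naturally to the second alternative, and change scores are not excluded. A reader might infer that the plan has chosen the wrong quantity for joint change. The text does not support that; it leaves the quantity open. This part of the objection stands.

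A reader might also take any correlation caused by stable differences between women as a false positive. It is not one when the question is association at a visit, which is a stated purpose. With a true baseline correlation of 0.4, r on baseline values is significant in about 85% of trials at N = 52, and that is power. The rates in step 1 are errors only if level correlations are reported as joint change.

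The arm problem is conditional as well. It cannot touch the two pre-intervention visits, and it needs arms that differ on both variables. Section 2.2 allows that the two treatments may have similar effects. It gives sizes only for NPRS and NDI, none for EMG, balance or kinesiophobia. At d = 0.5 the effect is small. Nor does the article say in words that the arms are pooled; it simply provides for nothing else.

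It can be argued too that adjusting for arm changes the estimand: if one treatment improves two outcomes, they do move together across the sample. But the separate between-arm comparisons already show that. What a correlation can add is linkage between individuals under the same treatment.

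Finally, a condensed article may leave detail to a fuller document. Silence alone would not be a point. Here a method is stated and attached to two purposes, and without an arm term it mixes arm contrast with individual linkage after baseline, whichever quantity is used.

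**Conclusion.** The point holds in limited form. One unadjusted coefficient is named for two questions, and the quantity correlated for each is not stated. For post-treatment data, levels or changes, r over both arms is not a test of individual linkage if the arms differ on both variables. At N = 52 the excess over 5% is slight at d = 0.5 (about 7% for levels, 10% for changes) and material at d = 0.8 (about 17% and 33%). These figures assume the same d on both variables and no relation within arm; the change-score figures also assume ICC 0.7.

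The documents do not support saying that the plan fixes the wrong test for joint change, or that its correlations are generally invalid. Correlation is not among the listed primary or secondary outcomes. The sample size and the primary comparison are unaffected. This is a cheap improvement to an exploratory analysis.

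**What to change.** Split the sentence in section 2.8 by purpose.
- **Joint change:** for each pair, the partial correlation, adjusted for randomised arm, of the changes from the second pre-intervention assessment to 4 weeks, reported with its 95% CI.
- **Association before treatment:** plain Pearson's r on levels, as now.
- **Association at a post-treatment visit:** r on levels adjusted for arm, described as association between levels and not as joint change.

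No new data are needed, since all outcomes are taken at both visits, and partial correlation is a standard procedure. The cost is a few lines of text, one degree of freedom (49 instead of 50 at N = 52), and the greater measurement noise of change scores, which will make some reported correlations smaller.

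### Clinical relevance is judged by partial eta squared, calculated only when significant: reported effect sizes are biased upward, and the index has neither direction nor clinical unit

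*Protocol article*

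**What the plan says.** Section 2.8 (Statistical Analysis) gives the purpose of the effect size: "In order to focus on clinical relevance or clinically worthwhile effects, and assess the magnitude of the change in the result variables". The measure is partial eta squared for the group × time repeated-measures ANOVA, calculated and graded "when significant, considering 0.01 small, 0.06 medium, and more than 0.14 large effect sizes".

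A second measure is optional: "we could use the Cohen d for any pairwise comparisons, when applicable". The same section runs pairwise comparisons after a significant interaction: "follow-up tests (post-hoc Sidak test) were performed to determine how the within-participant factors affected the dependent variables".

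The significance level is fixed in general terms, "The level of significance for the statistical tests were set at *p* ≤ 0.05 with a confidence interval of 95" per cent, without naming the estimate that the interval belongs to. Section 2.8 also provides, with no significance condition, for group means with SDs and for the change from baseline to 4 weeks by intention to treat for each outcome.

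Section 2.2 sizes the trial, "accepting an alpha risk of 0.05 and a beta risk of 0.2 in a two-sided test", to recognize a "difference greater than or equal to 2 units (SD = 1.75) (NPRS) or 7 units (SD = 6) (NDI"), together with a Cohen's d of 0.8.

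**The concern.** The sentence has two faults.

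- **Selection.** An effect size shown only after a significant test is drawn from the upper tail of its sampling distribution, so on average it overstates the truth. The overstatement is worst where power is low. Both arms are active exercise, and section 2.2 itself allows that GPR may have only similar effects, so true differences well below 0.8 are plausible. A non-significant comparison of two active treatments is also where the size of the difference matters most, and there the plan calculates no effect size.
- **Choice of index.** The primary objective asks which of two treatments is superior. Partial eta squared is a proportion of variance without sign. It cannot say which arm did better, and it is not in NPRS or NDI points.

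At stake is the trial's own statement on whether effects are worthwhile. The hypothesis tests are untouched.

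**Working it through.** **Inputs.** Two-sided alpha 0.05, power 0.80, d = 0.8, 26 evaluable per group, 15% loss and 62 recruited (section 2.2). Four time levels for pain intensity, CROM and PPT. Three for NDI and the other outcomes, which are not measured at the intermediate visit (sections 2.4 and 2.6).

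**Reproducing the plan's sample size.** A two-sample t-test with d = 0.8 needs 25.5, so 26 per group (power 0.807 at 26). Then 52/0.85 = 61.2, so 62. Both figures reproduce, and d = 0.8 is therefore taken as the design effect.

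**Step 1: smallest value that can be reported.** A significant interaction has F at or above F_crit, so the minimum is η²p = df1·F_crit/(df1·F_crit + df2), with df1 = levels − 1 and df2 = (N − 2)(levels − 1), sphericity assumed.

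| N | Time levels | df1, df2 | F_crit | Minimum η²p |
|---|---|---|---|---|
| 52 | 3 | 2, 100 | 3.087 | 0.058 |
| 52 | 4 | 3, 150 | 2.665 | 0.051 |
| 62 | 3 | 2, 120 | 3.072 | 0.049 |
| 62 | 4 | 3, 180 | 2.655 | 0.042 |

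For example, (3 × 2.655)/(3 × 2.655 + 180) = 7.965/187.965 = 0.042. By contrast, an observed 0.01 with N = 62 and four levels gives F = (0.01/0.99) × (180/3) = 0.61, far from significant.

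**Step 2: size of the selection.** As an illustration, take a 1-df contrast, the group difference in change. In simulated trials, t has non-centrality d√(n/2), the estimate is t√(2/n), and η²p = t²/(t² + 2n − 2). Results are averaged over all trials and over those with p < 0.05.

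| n per group | True d | Power | Mean d, all trials | Mean d, significant only |
|---|---|---|---|---|
| 26 | 0.3 | 0.19 | 0.30 | 0.71 |
| 26 | 0.5 | 0.42 | 0.51 | 0.77 |
| 26 | 0.8 | 0.81 | 0.81 | 0.91 |
| 31 | 0.3 | 0.21 | 0.30 | 0.66 |
| 31 | 0.5 | 0.49 | 0.51 | 0.72 |
| 31 | 0.8 | 0.87 | 0.81 | 0.87 |

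At d = 0.8 the excess is (0.91 − 0.80)/0.80 = 14% with 26 per group and (0.87 − 0.80)/0.80 = 9% with 31. At d = 0.3 the reported average is more than twice the truth, and about four in five such trials with 26 per group would show no effect size.

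On the plan's own index at 26 per group:

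| True d | Population η²p | Mean η²p, all trials | Mean η²p, significant only |
|---|---|---|---|
| 0.3 | 0.022 | 0.041 | 0.120 |
| 0.5 | 0.059 | 0.076 | 0.137 |
| 0.8 | 0.138 | 0.153 | 0.179 |

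Partial eta squared is somewhat high even without selection. The step from all trials to significant trials is the effect of the condition. With no true difference, significant results average 0.106, and about 13% of them exceed 0.14 and would be graded large.

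**Step 3: not a clinical scale.** Take SD = 1.75 at each time and a pre-post correlation ρ. The article gives no ρ, so 0.3 to 0.9 is assumed. The SD of change is 1.75√(2(1 − ρ)), the standardized difference is δ = 2/(SD of change), and for a two-time contrast η²p = (δ²/4)/(1 + δ²/4).

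- A 2-point NPRS difference gives 0.19 (ρ = 0.3), 0.25 (0.5), 0.35 (0.7) and 0.62 (0.9).
- The 0.14 cut for a large effect is reached at 1.67, 1.41, 1.09 and 0.63 points respectively.

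The same clinical difference can therefore give very different values, and over this range the large label is reached below the 2 points the trial was sized to detect.

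**The case against.** The strongest reply is that the condition touches only a supplementary index. Group means with SDs and the 4-week change are reported whatever the p-value, section 2.6.1 defines the primary outcome as change and between-group difference, and section 2.9 promises to publish negative and inconclusive results. That stands, and it rules out several stronger readings that a reader might infer.

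- *All information on non-significant outcomes is lost, and meta-analyses would receive selected estimates.* Not supported: a raw, unadjusted difference can be computed from the reported means, SDs and group sizes. Only the effect-size values are selected.
- *No effect can ever be graded small.* That would follow from a 1-df test, where the minimum is 0.075 (N = 52) or 0.063 (N = 62). The plan's interactions have 2 or 3 df, which leaves a narrow band from about 0.042 to 0.06.
- *The plan ignores its own clinical-relevance thresholds.* Section 2.2 presents 2 and 7 units as differences to be detected. It does not call them thresholds of relevance.

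It may also be said that the details of a difference with its interval belong in a fuller analysis plan. That is fair for the details, but the article itself states the significance condition and the choice of index.

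Cohen's d does not repair this. It is optional, also standardized, and confined to pairwise comparisons that follow a significant interaction.

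**Conclusion.** The point holds as a fault in how magnitude and clinical relevance are to be reported. Selection raises the reported standardized effect by about 9 to 14% at the design effect, by about 44 to 54% at a true d of 0.5, and to more than double at 0.3. If the true effect were as large as the raw inputs in section 2.2 imply (2/1.75 = 1.14; 7/6 = 1.17), power at 26 per group would be about 0.98 and selection would hardly matter.

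These figures rest on a 1-df contrast with normal data and serve as illustration. They are averages over significant results, so they do not show that any given outcome will be overstated. The minima of 0.042 to 0.058 assume sphericity; a sphericity correction would raise them. The lack of direction and clinical unit needs no assumption. The change is worth making, but it does not affect the validity of the tests.

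**What to change.** In section 2.8:

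1. Delete the condition that the effect size is calculated only if the test is significant.
2. State that, for every outcome and whatever the p-value, the magnitude of effect is the GPR minus STE difference in change from baseline (the second pre-intervention assessment) to 4 weeks, with its 95% CI in scale units.
3. Read the NPRS and NDI differences and their intervals against the 2 and 7 units that the trial was sized to detect, described as such. If the authors hold a separate threshold of clinical relevance, they should state it with its source. Say whether NDI is in points or per cent, since section 2.6.1 mentions both.
4. Keep partial eta squared, if wanted, as a supplement reported for all outcomes and not described as clinical relevance.

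The cost is a few sentences and a table column. It needs no new data, no further participants and no change to the hypothesis tests.
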